***2.9 Neurochemical Measurements***

DNMT, TET, Glucorticoid receptor, BDNF, and related mRNA's will be assessed in lymphocyte samples draw at b baseline and week 8 of study.

***A) Preparation of Lymphocytes***

Lymphocytes will be isolated with the Ficoll-Paque Plus method and reagents using the Amersham Kit (Biosciences2001-2006). Defibrinated or anticoagulant-treated blood is layered on the Ficoll-Paque PLUS solution and centrifuged for a short period of time. Different migration during centrifugation results in the formation of layers containing different cell types. The bottom layer contains erythrocytes which have been aggregated by Ficoll, and, therefore, sediment completely through the Ficoll-Paque PLUS. The layer immediately above the erythrocyte layer contains mostly granulocytes which, at the osmotic pressure of the Ficoll-Paque PLUS, attain a density great enough to migrate through the Ficoll-Paque PLUS layer. Because of their lower density, the lymphocytes are found at the interface between the plasma and the Ficoll-Paque PLUS with other slowly sedimenting particles (platelets and monocytes). The lymphocytes are then recovered from the interface and subjected to short washing steps with a balanced salt solution to remove any platelets, Ficoll-Paque PLUS and plasma. Since this method can be adapted to very small volumes of blood, it is particularly suitable for isolation of lymphocytes where only limited quantities of blood are available.

**B) *RNA Extraction***

Total RNA from lymphocyte was isolated using the TRIzol reagent (Life Technologies 15596-026; Life Technologies Corporation, USA; Mannhalter et al., 2000) and further purified using the Qiagen RNeasy Kit (Qiagen, Valencia, CA, USA***C)***

***C) Real-time polymerase chain reaction (PCR) quantification***

Total RNA was converted to cDNA using the Applied Biosystems (USA) High Capacity Archive Kit (4368813). Relative quantitative real-time polymerase chain reaction (qPCR) was performed with the Applied Biosynthesis Real-Time PCR system using Fermenta Maxima SYBR Green/ROX qPCR Master Mix (K0222; Fermentas International Inc., Canada). PCR mixtures were run on a Stratagene (USA) Mx3005P QPCR System. Primers were designed to cross over one intron to amplify cDNA and yielding an amplicon of between 75-200 base pairs. Dissociation curves were conducted to establish the presence of a single amplicon at the predicted melting temperature and a lack of primer-dimer formation. A comparative threshold cycle (CT) validation experiment was done to determine target and reference primer efficiency. For normalization of mRNAs expression, β-actin and GAPDH were used as internal controls. For the respective housekeeping genes, we measured the gene stability using the NormFinder alogaithm ((Andersen CL, Jensen JL, Orntoft TF, Normalization of real-time quantitative reverse transcription-PCR data: a model-based variance estimation approach to identify genes suited for normalization, applied to bladder and colon cancer data sets, Cancer; 64:5245-5250, 2004), which allows the identification of the best and suitable housekeeping gene for data normalization. For the respective genes studied, our preliminary data showed similar results when the data was normalized to -actin or GAPDH, and because -actin had the highest housekeeping gene stability (NormFinder), we normalized our data to -actin. CT value was used for relative quantification of target gene expression and normalized to -actin and the relative expression levels were calculated as CT (Livak & Schmittgen, 2001, Schmittegen & Livak, 2008). **2**.

***2.10 Outline of Research Evaluation Schedule***

A) Pre- consent screening -Screening-Chart review of medical and psychiatric diagnosis, and psychopathology and behavior.

*B) Consent*- RBANS, PANSS, CALGARY DEPRESSION, Modified SANS Scale, smoking surges scales

*C)Baseline*- MATRICS Cognitive Battery, Cigarette Dependence Scale, Current Smoking questionnaire, Plasma Sample for Nicotine-Cotinine, Blood Sample for determination of α7 mRNA and DNMT1 and GAD67 mRNA’s in lymphocytes .Side-effect checklist.

DNA Sample may be collected at baseline or any later point if the subject consents to this additional procedure.

*D)Weekly*- weekly interview, with questioning of major changes in psychiatric status or side effects, drug distribution, counting of pills from previous week.

*E)Week 2*- side-effects checklist

*F)Week 4,8*- PANSS, Calgary Depression Scale, side effects checklist, nicotine-cotinine sample, smoking urges scale, side-effects checklist.

*G)Week 8-12* -PANSS, Calgary Depression Scale, side-effects checklist list, Blood Sample for determination of α7 mRNA and DNMT1 and GAD67 mRNA’s in lymphocytes, smoking urges scale , MATRICS Cognitive Battery, Modified SANS, Cigarette Dependence Scale, Current Smoking questionnaire, Plasma Sample of Nicotine Cotinine, side effects checklist.

***2.11*** ***Criteria for subject termination from study***

Subjects will be terminated from participation in the study if they develop severe nausea or vomiting which does not show tolerance over the first four weeks of treatment, or if they request discontinuation because of this side-effect. Subjects will also be terminated if their PANSS scores show a 35% or greater increase on two consecutive ratings, including at least a 30% increase in positive symptoms, and a CGI score of much worse. They will be also be terminated if the treating physician believes their clinical condition has gotten much worse and requests discontinuation. If the subjects Calgary Depression Scale score increases by >50% on two consecutive ratings, and sum is also > 16, the patient will be terminated from the study. They will also be discontinued if they have persistent suicidal ideation or make a suicidal attempt or gesture. If the patient exhibits a marked increase in psychotic or depressive symptoms from the previous week, which is considered immediately clinically significant and threatening to his life or continued functioning or requiring immediate rehospitalization, the patient will be terminated from the study. If he makes a serious suicidal gesture or attempt in the prior week or expresses definite suicidal intent he will be immediately terminated from the study. Furthermore, subjects have the right to withdraw consent at any time.

***2.12 Subject Payments***

Subjects who sign consent and complete the RBANS will be paid $15. Subjects included in the treatment trail will be paid $15 per week for each week that they cooperate with all standard procedures of the study. They will be paid an additional $10 for the baseline and end of study blood samples. They will be paid an additional $5 for completing a neuropsychological battery test session. For subjects who are not inpatients at MPC or residing on the grounds transitional residence will be paid up to $10 for each occasion they need to make special trips to a site for study research procedures in order to cover transportation costs. Subjects are paid $5 if they agree to the genetic sample. Payment levels for outpatients are slightly greater than for inpatients.

**III STATISTICAL ANALYSIS**

***3.1 General***

The primary dependent outcome variable, will be the average score on all tests of MATRICs battery (converted to T scores from different tests). Secondary cognitive analysis will be the of the hypothesized effects of attention-vigilance, verbal memory, and visual spatial memory. Secondary outcome variables will be cigarette smoking variables( cigarettes smoked, CO, nicotine and cotinine in plasma, smoking scores, Calgary depression scores).The general analysis approach will use a repeated measures analysis of variance. If there are appreciable missing data on measures with several ( >2) sequential testings a mixed model analysis will be used. If the data deviates significantly from normality, a non-parametric approach may be utilized using Wilcoxon matched pair’s signed-ranks, or Friedman’s two way analysis of variance. To examine whether there are differences in effects in patients with different degrees of cigarette smoking, we will compare smoking measures in patients assigned to placebo or active drug, and correlate effects on neuropsychological test changes with the smoking measures described above. Paired T-tests, or repeated measures ANOVA, will be used to analyze differences in the biochemical measures. Pearson or Spearman correlations will be used to examine the relationship between baseline neurochemical measures to cognitive tests performed at baseline, and both baseline neurochemical measure and change in these measures will be correlated with change in neuropsychological test scores. Additional analyses may use these neurochemical measures or changes during treatment as a covariate in an overall repeated measures analysis of variance.

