**II RESEARCH PLAN**

***2.1 General Overview.***

This will be an 8 week parallel group placebo controlled double-blind experimental design in which cognitive function and psychopathology will be evaluated in schizophrenics (DSM IV diagnoses of schizophrenia or schizoaffective disorder). (Extension to 12 weeks at some sites including NKI site for smoking and psychopathology measures.) Patients will be tested on the MATRICS cognitive battery. Psychiatric status will be evaluated with the PANSS scale. Depression and any emerging suicidal ideation will be assessed by the CALGARY Depression scale. Negative symptoms for alogia and anhedonia will be assessed at beginning and end by abbreviated sections of the SANS scale. Changes in methylating enzyme functions related to GABAergic function will be assessed by measuring DNMT1 and GAD67 mRNAs in lymphocytes. These measures will be correlated with cognitive changes produced by varenicline. Because many schizophrenic patients are chronic cigarette smokers, and varenicline also affects cigarette smoking, cigarette smoking will be monitored by smoking questionnaires and nicotine and cotinine in plasma.

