***2.6 Cognitive evaluations***

A) The patient will be evaluated with the RBANS to see if he qualifies on cognitive scores as defined in inclusion criteria. He will be given a brief trial on the Matrix mazes to reduced practice effects on this test.

B) Patients who qualify on the basis of RBANS scores will be administered the MATRICS Cognitive battery at baseline and last month of study. The MATRICS Battery is an expert consensus cognitive battery which has been developed to be used in studies of psychoactive drugs that may benefit cognition in schizophrenia. The Social Cognition MSCEIT will be excluded because of previously documented difficulty in administering this to seriously ill schizophrenic patients and questions about its usefulness and validity.

C) At the U.S. sites another measure of spatial memory was added, and computer navigation task ( 'water task') which is a human analogue of a spatial memory task sued in many animal studies.

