***Amendments to IRB Protocol***:

Summary of Amendments

*Amendment 1*: Modification of risk statements in consent form in response to discussion with FDA

*Amendment 2:* Addition of MATRICS Battery of neuropsychological test-

*Amendment 3*: Additional survey questions and proposed advertising flyer

Amendment 4: Minor changes in procedures; coordination with Stanley Grant; addition of inpatients.

*Amendment 5*: Addition of family history data and smell test (This part of protocol was not carried out extensively because of lack of funding for smell test battery).

*Amendment 6*: Approval of Israeli Collaborative Site.

*Amendment 7:* Approval of NKI collaborative site.

*Amendment 8*: Addition of Baseline/screening EKG test at start of study, minor changes in cardiac

Exclusion criteria and expansion to involve RPC inpatient subjects on CREF.

Amendment 9-*Spatial Memory Task In 'Controls*

The object of this amendment is to compare performance on the *Virtual Morris Water Maze Task*, a measure of spatial memory, memory task, that we have obtained dint he original main protocol, to normal controls, who will be the subject of this amendment.

Subjects:

The subjects for this sub study will be male and female controls, 21-65 years of age who do not have a diagnosis of schizophrenia or psychotic disorders, major depressive disorder, bipolar disorder, ADHD, autism spectrum disorder downs syndrome, or dementia or Alzheimer's disease. They will not be currently taking antipsychotic, antidepressant, amphetamines or ADHD medication or varenicline. They will not have a major neurological illness for which they are currently being treated with medication or electrical or prior surgical therapy. 15 subjects will be cigarette smokers and 15 subjects will be current non-smokers. Assuming a 10-15% drop out rate, to obtain 30 valid subjects we may enroll or consent up total of 35 subjects.

Subjects Recruitment:

Subjects will be recruited from NKI research outpatient clinic control pool and volunteers, students and staff members of Nathan Kline Institute and Rockland Psychiatric Center. If we do not find enough subjects from these sources and want to recruit from a larger pool from Rockland County through advertisements, we will submit an advertisement for approval to the NKI IRB.

Procedures:

1. The patient will have brief interview and fill out questionnaires to assessing his medical and psychiatric history, current treatments, medications, and cigarette smoking.

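### The primary MATRICS score is measured twice, so the planned repeated measures ANOVA is at best a change-score test; ANCOVA with baseline as covariate is more precise at no extra data cost

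*Protocol*

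**What the plan says.** Protocol section 3.1 defines the primary outcome as the "average score on all tests of MATRICs battery (converted to T scores from different tests". It then sets one method for the outcomes in general: "The general analysis approach will use a repeated measures analysis of variance".

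Section 2.6 fixes the number of measurements. Qualifying patients are "administered the MATRICS Cognitive battery at baseline and last month of study", and the schedule in 2.10 agrees, with one battery at baseline and one in the week 8–12 block.

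The alternative model in 3.1 does not reach this outcome: "If there are appreciable missing data on measures with several ( >2) sequential testings a mixed model analysis will be used". Covariates are mentioned only for a different purpose: "Additional analyses may use these neurochemical measures or changes during treatment as a covariate in an overall repeated measures analysis of variance". The models described in 3.1 contain neither the baseline MATRICS score nor site, and 3.1 does not say which term of the repeated measures ANOVA is the test of treatment.

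The trial has several sites. Section 2.1 refers to an "Extension to 12 weeks at some sites including NKI site for smoking and psychopathology measures", and the amendment list records "Approval of Israeli Collaborative Site".

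**The concern.** A repeated measures ANOVA with two groups and two occasions gives three F tests: group, time, and group by time. Only group by time asks whether the arms changed differently, and with two occasions it is the square of the t statistic on change. A change score subtracts the whole baseline value, whereas the best linear predictor of the end score subtracts only a fraction r of it (equal variances). The excess is noise. ANCOVA estimates that fraction and removes the excess.

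What is at stake is precision on the primary outcome of a small trial, obtainable from scores that are collected anyway. A second matter is that the unnamed test term leaves room for a much weaker test, the group main effect, which averages a pre-treatment score into the outcome.

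**Working it through.** **Inputs from the protocol.** Two measurements (2.6, 2.10); α = 0.05 (3.2; sidedness not stated, two-sided assumed); 30 per arm (3.2); dropout 10–20% (2.2); enrolment of up to 100 allowed (2.2).

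**Assumed.** r is not given, so a range is shown. No SD or absolute difference is given, so effects d are in SD units of the end score, with equal variance at both visits. Assignment is taken as random.

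**The plan's own figure.** Section 3.2 gives 15 or 29 per group for 80% power under a two-group univariate ANOVA. Without an SD this cannot be reproduced directly. Solved backwards (two-sided t-test), 29 per group implies d = 0.75 and 15 per group implies d = 1.06.

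**Sample size.** 60 × 0.9 / 2 = 27 per arm and 60 × 0.8 / 2 = 24 per arm. If 100 were enrolled, the same dropout leaves 45 and 40 per arm.

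**Variances, in units of the end-score variance.**
- Change score (group by time): 2(1−r)
- ANCOVA: 1−r² = (1−r)(1+r)
- Ratio, ANCOVA to change: (1+r)/2, below 1 for every r below 1

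**Power at 27 per arm, d = 0.5.** Noncentral t with noncentrality d / √(V × 2/27), where V is the variance above; 52 degrees of freedom for change and 51 for ANCOVA.

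| r | Variance ratio | Noncentrality, change → ANCOVA | Power, change → ANCOVA |
|---|---|---|---|
| 0.5 | 0.75 | 1.84 → 2.12 | 43.8% → 54.8% |
| 0.7 | 0.85 | 2.37 → 2.57 | 64.3% → 71.4% |
| 0.8 | 0.90 | 2.90 → 3.06 | 81.3% → 85.2% |
| 0.9 | 0.95 | 4.11 → 4.22 | 98.1% → 98.5% |

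At 24 per arm the first three rows become 39.6% → 49.9%, 59.1% → 66.0% and 76.5% → 80.6%.

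**The same at d = 0.75**, 27 per arm: 77.2% → 87.7% (r = 0.5), 93.7% → 96.6% (0.7), 99.0% → 99.5% (0.8).

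**Without choosing d.** If the change-score test has 80% power at 30 per arm, ANCOVA has 89.9%, 85.9%, 83.9% and 82.0% at r = 0.5, 0.7, 0.8 and 0.9. It reaches 80% with 23, 26, 28 and 29 per arm, against 30–31.

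**Group main effect.** The mean of the two visits carries an effect of d/2 with variance (1+r)/2. At d = 0.75 and 27 per arm, power is 34.5%, 31.1% and 29.7% at r = 0.5, 0.7 and 0.8.

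**Site.** In a simulation with three sites, 30 per arm, d = 0.5 and a between-site SD of 0.4, adding site to ANCOVA moved power from 56.8% to 57.5% at r = 0.5 and from 88.5% to 88.4% at r = 0.8 (2,000 runs each).

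**The case against.** The strongest reply is that nothing here is invalid. With random assignment, the group-by-time test is unbiased and keeps its type I error. A reader might infer that the primary analysis is biased or wrong; the protocol does not support that, and the loss is one of precision only. This part of the reply stands.

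The size is also uncertain. Neither r nor d is documented, and at r = 0.9 the saving is about 5% of variance. At the effects implied by 3.2 the gain is small once r is 0.8 or more. Estimating the slope inflates the ANCOVA variance by about 2% with 54 patients, so at r above roughly 0.96 ANCOVA would lose slightly. And 27 per arm belongs to the 60-patient target, not to the enrolment ceiling of 100. All of this stands, and it is why the gain is given as a range.

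Two stronger readings do not hold:
- That leaving out site costs appreciable power. A constant site shift cancels in a change score, the simulation moved by less than one point, and the protocol gives no between-site variance. Site terms are also commonly left to an SAP.
- That the group main effect will be read. Section 3.1 does not say so, and it elsewhere speaks of change in test scores. The 30–35% figure shows what an unnamed term could permit, not what is planned.

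Finally, an SAP could refine a general approach. But 3.1 is not silent: it names a method and limits the mixed-model alternative to measures that do not include the primary outcome.

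**Conclusion.** The point holds as a matter of efficiency and specification. For a primary outcome measured twice, section 3.1 sets a method whose relevant test is a change-score t-test. ANCOVA on the same patients and the same two scores removes 25% of the variance at r = 0.5, falling to 5% at r = 0.9. At 27 per arm and 0.5 SD, that is about 11 points of power at the low end of the range and less than one at the high end.

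This rests on random assignment, which the protocol implies by a double-blind, placebo-controlled, parallel-group design but does not state in so many words, and on assumed values of r and d. The gain comes from the baseline covariate. The treatment term should be named whichever model is kept.

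**What to change.** In section 3.1, state the primary test as an ANCOVA of the end-of-treatment MATRICS average T score on treatment and baseline MATRICS average, reporting the adjusted treatment difference with its 95% CI. This also settles which term is the test of treatment. Use the same form for other between-group outcomes measured at two points, such as the modified SANS.

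Site may be added to the model as a design factor, justified by the multi-site conduct and not by power.

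The cost is a sentence or two in the protocol, one degree of freedom for baseline and, if site is included, one for each site beyond the first. No new data, visits or patients are needed.

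### The non-parametric fallback, and the paired t-tests for the biochemical measures, contain no varenicline-versus-placebo comparison

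*Protocol*

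**What the plan says.** Protocol section 2.1 describes an "8 week parallel group placebo controlled double-blind experimental design", so each patient receives either varenicline or placebo. Section 3.1 sets the default: "The general analysis approach will use a repeated measures analysis of variance", with a mixed model if appreciable data are missing on measures tested more than twice.

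The same section then gives the rule for non-normal data. It begins "If the data deviates significantly from normality, a non-parametric approach may be utilized using Wilcoxon matched" and goes on to matched-pairs signed-ranks or "Friedman’s two way analysis of variance". The rule is not limited to any outcome, and the protocol names no rank test that compares the two arms.

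For the laboratory measures, section 3.1 says: "Paired T-tests, or repeated measures ANOVA, will be used to analyze differences in the biochemical measures".

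Two further statements matter. Under section 2.6, patients are "administered the MATRICS Cognitive battery at baseline and last month of study", so the primary outcome has two test occasions. Section 2.6 also recognises practice effects on one MATRICS component: "He will be given a brief trial on the Matrix mazes to reduced practice effects on this test".

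**The concern.** The trial asks whether patients on varenicline change more than patients on placebo. A signed-rank test, a Friedman test and a paired t-test each compare values from the same patient at different visits. Treatment arm does not enter any of them.

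If one of these tests is used for inference, there are two ways to run it, and neither tests the drug:

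- **Pooled over arms**, it asks whether scores changed at all. A practice gain shared by both arms is enough to make it significant.
- **Run separately by arm**, it invites the conclusion that the drug works because the change is significant on varenicline and not on placebo. That is not a test of the difference between arms.

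The placebo group, which is there to remove practice and time effects, then no longer does so. The protocol is not silent here, leaving detail to a later SAP. It names specific tests, and a SAP that followed the text would carry the fault forward.

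**Working it through.** **1. What each named test compares**

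| Test in section 3.1 | Factors in the test | Varenicline-versus-placebo term |
|---|---|---|
| Repeated measures ANOVA / mixed model (default) | visit, and arm if included | yes, through group-by-time |
| Wilcoxon matched-pairs signed-ranks | visit within patient | none |
| Friedman | patient and visit (these are the two ways) | none |
| Paired t-test (biochemical) | visit within patient | none |

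With only two MATRICS occasions, Friedman reduces to a sign-type test of before against after.

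**2. The plan's own figure**

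Section 3.2 gives 15 or 29 per group for 80% power at α = .05 and a 28% or 18% improvement over placebo, under a two-group model. No SD is stated, so the figure cannot be reproduced from stated inputs. With a two-sided two-sample t-test, n = 15 and 29 imply standardised differences of 1.06 and 0.75. An assumed SD of 23.5% to 24.5% of the placebo mean gives 13–14 and 28–31 per group, close to the stated values. The sizing is therefore compatible with a between-arm test, which is the comparison the fallback drops.

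**3. Illustration with no drug effect**

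Inputs: 27 valid patients per arm (30 per arm from section 3.2, less 10%, the lower end of the dropout range in section 2.2); two-sided 0.05; change scores N(g, 1) in both arms. The shared gain g, in SD of the change score, is an assumption; the protocol gives no value.

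A normal approximation for the signed-rank test is: rejection rate ≈ Φ(g√(3n/π) − 1.96).

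Pooled, n = 54, √(3 × 54/π) = 7.18:

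- g = 0.2: Φ(1.436 − 1.96) = Φ(−0.524) = 0.30
- g = 0.35: Φ(2.513 − 1.96) = Φ(0.553) = 0.71
- g = 0.5: Φ(3.590 − 1.96) = Φ(1.630) = 0.95

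Simulation (3,000 trials each) gives 29%, 70% and 94%.

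By arm, n = 27, √(3 × 27/π) = 5.08. At g = 0.35 each arm is significant with probability Φ(1.777 − 1.96) = Φ(−0.183) = 0.43. The pattern of significant on varenicline and not on placebo then has probability 0.43 × 0.57 ≈ 0.24, and simulation also gives 24%.

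The between-arm rank-sum test on change rejects near 5% at every g, because the shared gain cancels.

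**4. A second parameterisation**

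Here there are 30 per arm, the gain is in SD of the score itself, and the test-retest correlation ρ is assumed to be 0.7, 0.8 or 0.9. The SD of change is √(2(1 − ρ)) = 0.77, 0.63 or 0.45. A gain of 0.2 SD is then 0.26, 0.32 or 0.45 SD of change. Simulated rejection rates with no drug effect at that gain:

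| ρ | Signed-rank, varenicline arm | Signed-rank, pooled | Rank-sum between arms |
|---|---|---|---|
| 0.7 | 28% | 49% | 4.5% |
| 0.8 | 40% | 67% | 5.3% |
| 0.9 | 65% | 92% | 5.7% |

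Friedman over three visits in one arm of 30 (ρ = 0.8) rejects in 24%, 48% and 91% of trials for a total shift of 0.2, 0.3 and 0.5 SD.

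**5. Biochemical measures**

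These simulations do not apply here, since practice does not act on mRNA. The logical point remains: a paired t-test shows only change from baseline, and drift over time or a change in smoking would contribute to it.

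**The case against.** The main analysis is sound. Repeated measures ANOVA or a mixed model can carry group-by-time. Section 3.2 sizes the trial on active versus placebo, and section 3.1 says smoking measures will be compared between patients assigned to the two treatments. The intent to compare arms is clear. The fallback needs a significant departure from normality, and even then it only may be used. A reader might infer that the protocol will credit practice effects to varenicline, or that the primary analysis is invalid. The text supports neither: it nowhere says that a within-patient p-value will be taken as the drug effect.

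The primary outcome is also an average of T scores over several tests, which makes a marked departure from normality less likely there. The biochemical measures are listed as neither primary nor secondary outcomes, and repeated measures ANOVA is offered in the same sentence as the paired t-test.

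The percentages are illustrative. The gain, the 27 per arm and the pooling over arms are assumptions, and the protocol's one remark on practice concerns a single test for which it takes a precaution. The simulated data are normal, so the rates describe the tests once used, not the whole conditional procedure.

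All of this stands, and it limits the severity. It does not rescue the named tests. When the fallback is used, it gives the wrong comparison. Skewed or zero-heavy smoking data are plausible, because section 2.2 admits patients who are not smoking daily in a non-smoking facility and the nicotine and cotinine assays have lower limits (Cigarette Smoking Assessments).

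**Conclusion.** The point holds as a fault in the stated fallback and in one of the two options for the biochemical measures. The tests named cannot compare varenicline with placebo, and this follows from the design without any assumption. The default analysis is not affected, provided group-by-time is the test of the drug.

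The size depends on the shared change over time, which the documents do not give. For assumed gains of 0.2 to 0.5 SD of the change score and 27 per arm, the pooled signed-rank error is about 29% to 94%, against about 5% for a between-arm rank-sum test. These are hypothetical rates, not error rates of the trial's plan as a whole. Because the fallback is optional and the default is valid, this is a should-fix.

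**What to change.** In section 3.1:

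- Replace the matched-pairs and Friedman fallback with a between-arm rank method, such as Wilcoxon rank-sum on change scores or rank ANCOVA adjusted for baseline.
- State that the group-by-time term is the test of the drug in the repeated measures ANOVA or mixed model.
- For the biochemical measures, replace paired t-tests as the test of drug effect with a between-arm contrast: group-by-time, or ANCOVA of the end-of-treatment sample on its baseline value, on the log scale if skewed. First reconcile the sample time, since section 2.9 gives week 8 and section 2.10 G gives weeks 8–12.
- Keep paired tests as within-arm description only.

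The cost is a change of wording; no new data are needed.
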